**Methods:**

*Study design*: Prospective, single-blind, parallel-group, multi-centre randomised controlled trial.

*Settings*: The computer-aided system ENDOANGEL-GC was used to monitor blind spots, detect gastric abnormalities, and identify gastric neoplasms during EGD.

*Participants*: Adults who underwent screening, diagnosis, or surveillance EGD.

Randomisation groups:

1. Experiment group, EGD examinations with the assistance of the ENDOANGEL-GC;

2. Control group, EGD examinations without the assistance of the ENDOANGEL-GC.

*Randomisation*: Block randomisation, stratified by centre.

*Primary outcomes*: Detection rates of gastric neoplasms and EGC.

*Secondary outcomes*: Detection rate of premalignant gastric lesions, biopsy rate, observation time, and number of blind spots on EGD.

*Blinding*: Outcomes are undertaken by blinded assessors.

*Sample size*: Based on the previously published findings and our pilot study, the detection rate of gastric neoplasms in the control group is estimated to be 2.5%, and that of the experimental group is expected to be 4.0%. With a two-sided α level of 0.05 and power of 80%, allowing for a 10% drop-out rate, the sample size is calculated as 4858. The detection rate of EGC in the control group is estimated to be 20%, and that of the experiment group is expected to be 35%. With a two-sided *α* level of 0.05 and power of 80%, a total of 270 cases of gastric cancer are needed. Assuming the proportion of gastric cancer to be 1% in patients undergoing EGD and allowing for a 10% dropout rate, the sample size is calculated as 30,000. Considering the larger sample size calculated from the two primary endpoints, the required sample size is determined to be 30,000.

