With the rapid progress in artificial intelligence (AI) technology, several researchers have developed intelligent systems aimed at diagnosing EGC or upper gastrointestinal neoplasms, and few studies have aimed to ensure the completeness of examinations [14, 15]. In 2019, we first applied deep learning algorithms to the field of endoscopy quality control. We developed WISENSE (renamed ENDOANGEL), an intelligent system aimed at monitoring blind spots in upper gastrointestinal endoscopy in real time [16]. Single-centre and multi-centre randomised controlled trials (RCTs) have proven to significantly reduce the blind spot rate in examinations. Furthermore, we developed ENDOANGEL-LD (lesion detection) to detect gastric abnormalities and diagnose gastric neoplasms (low-grade dysplasia, gastric adenomas, gastric lymphomas, EGC, and advanced gastric cancers) in real time [17]. In another single-centre, tandem-designed trial, we proved that ENDOANGEL-LD could reduce the biopsy rate and miss rates of gastric neoplasms in real time [18].

Development of a tool with the ability to simultaneously improve the diagnostic performance of WLE and ensure high completeness of examination is an ideal way to fulfil these needs. Therefore, we proposed the AI system ENDOANGEL-GC (gastric cancer), which simultaneously combines the functions of blind spot monitoring and lesion detection and runs in real time. We designed this randomised, controlled, patient-blinded, multi-centre trial with two parallel groups and a 1:1 allocation to evaluate the hypothesis that ENDOANGEL-GC would improve the detection rates of gastric neoplasms and EGC.

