The endoscopists who participate in the study are required to have EGD experience with more than 500 cases. All participating endoscopists will be trained in the AI’s functions, including monitoring anatomical landmarks, detecting suspicious lesions, and becoming familiar with the operation requirements during endoscopy. Each endoscopist will perform at least 10 examinations with AI assistance. In both groups, endoscopists are required to screen the entire stomach under white light mode. Only when the screening process is completed and suspicious lesions are found, the image-enhanced mode will be allowed for further judgement. In the experimental group, the endoscopists will operate the endoscope with the assistance of ENDOANGEL-GC. They are required to adhere to the following criteria: (1) screen anatomical landmarks according to the feedback of ENDOANGEL-GC and (2) lesions marked in red boxes by ENDOANGEL-GC are required to undergo biopsy sampling. Lesions that are not marked in red boxes but meet any of the following criteria are also recommended for biopsy: differences in colour, loss of vascularity, slight elevation or depression, nodularity, thickening, abnormal convergence or flattening of folds, irregular margins, irregular discoloration, or irregular surfaces. In the control group, endoscopists will routinely operate on the endoscope. Lesions that meet the above criteria are also recommended for biopsy.

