### Specimen management and pathological traceability

After tissue sampling, the specimens that arrive in the pathology department will be dehydrated, embedded, sliced, and stained. Pathological results will be obtained from local study centres by expert pathologists at each centre. Regarding patients diagnosed with gastric cancers by biopsy and those highly suspected with gastric cancer without biopsy who will possibly take further elective operations, their pathological results of resected specimens will be traced for up to 60 days from their endoscopy date to determine the invasion depth of gastric cancer.

After the training program, a group of five research assistants will watch the raw video of each participant and capture clean, high-quality frames of the lesions with pathological results under the guidance of an expert endoscopist. All images of the lesions and corresponding pathological results will be sent to an independent group of three expert endoscopists for further endoscopic evaluation. Randomisation and personal information will be concealed, and the experts will be unaware of the allocation of the lesions. A group of three experts will evaluate the endoscopic and pathological diganosis of a lesion and determine whether they are unmatched. (Here was a clerical error of describing the determination of the unmatched lesions, and we have corrected it). De-identified digital pathological slides of unmatched lesions will be sent to an independent group of expert pathologists for consultation. Only unmatched lesions will be reviewed by an independent group of expert pathologists for the final diagnosis.

Each expert pathologist is required to determine whether the slide contains acute inflammation, chronic inflammation, atrophy, or intestinal metaplasia and to rate the severity (mild, moderate, or severe) of these pathological changes. In addition, they are required to determine the presence of low-grade intraepithelial neoplasia, high-grade intraepithelial neoplasia, or carcinoma. Multiple pathological changes may occur in the same lesion, the most severe being the primary diagnosis. The severity of the pathological changes increases from inflammation to carcinoma. A lesion is diagnosed only when two or more experts reach a consensus. If the three expert pathologists did not reach a consensus, the lesion was re-evaluated until a consensus was reached.

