## Outcomes

The primary outcome measures are detection rate of gastric neoplasms and EGC detection rate. The gastric neoplasm detection rate is defined as the ratio of patients with neoplasms to the recruited population. The EGC detection rate is defined as the ratio of patients with EGC to all patients with gastric cancer. EGC includes pathologically proven high-grade intraepithelial neoplasia and gastric cancer restricted to the mucosa and submucosa.

Secondary outcome measures include the detection rate of premalignant gastric lesions, biopsy rate, observation time, and number of blind spots on EGD examination. The detection rate of premalignant gastric lesions was defined as the ratio of patients with premalignant gastric lesions to the entire recruited population. The biopsy rate is defined as the ratio of patients who undergo biopsy in the recruited population. The observation time is defined as the overall examination time under WLE minus the biopsy operation time. Blind spots are defined as unobserved landmarks.

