## Data analysis

### Sample size calculation

The sample size is calculated on the basis of the primary outcomes.

The detection rate of gastric neoplasms and EGC detection rate without AI assistance were determined by literature research. Zhang et al. reported an EGC detection rate of 20.0 to 20.9% [21] and a gastric neoplasm detection rate of 1.63%. Di et al. reported an EGC detection rate of 16.44% and a gastric neoplasm detection rate of 3.37% [22]. Therefore, the EGC detection rate in the control group is estimated to be 20%, and the gastric neoplasm detection rate is estimated to be 2.5% (the mean value of the two references).

According to our previous study, the detection rate of gastric neoplasms increased by 1.35% when assisted by an AI system; therefore, the detection rate of gastric neoplasms in the experimental group is estimated to be 4.0%. There are no published data evaluating the improvement in EGC detection rates with AI assistance. Thus, we referred to two studies reporting improvements of > 80% in EGC detection sensitivity and proportion [23, 24], resulting in an estimation that the EGC detection rate will increase from 20% to 35% with AI assistance.

The sample size was calculated, using the *Z* test method, as 4858 based on the detection rate of gastric neoplasms, with a two-sided *α* level of 0.05 and power of 80%, allowing for 10% drop-out rate. Regarding the sample size based on the EGC detection rate, the *Z* test method was used for calculation with a two-sided *α* level of 0.05 and power of 80%, resulting in a total of 270 cases of gastric cancer. Assuming the proportion of gastric cancer to be 1% in patients undergoing EGD and allowing for a 10% dropout rate, the sample size was calculated as 30,000. Considering the larger sample size calculated from the two primary endpoints, the required sample size was determined to be 30,000.

To achieve adequate participant enrolment, we first evaluated the annual volume of sedated EGD examinations at all participating centres. The sum of the examination volumes of all centres (> 20,000 per year) is sufficient to provide support for the completion of the study. In each centre, a study coordinator, group of nurses, or endoscopists will be pretrained for informed consent before the examination. Consecutive patients will be informed about the study and assessed for eligibility.

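### The EGC co-primary divides by the gastric cancers each arm detects, a count the AI may change, so once the AI has an effect the ratio cannot by itself be read as improved EGC detection

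*Protocol article*

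**What the plan says.** The Outcomes section gives the two primary outcomes different denominators. For neoplasms: "The gastric neoplasm detection rate is defined as the ratio of patients with neoplasms to the recruited population". For EGC: "The EGC detection rate is defined as the ratio of patients with EGC to all patients with gastric cancer". The premalignant-lesion rate and the biopsy rate also use the recruited population. No EGC rate per randomised patient appears among the primary or secondary outcomes.

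Four other places bear on the EGC denominator:

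- **Introduction.** The earlier lesion-detection system is described as able to "diagnose gastric neoplasms (low-grade dysplasia, gastric adenomas, gastric lymphomas, EGC, and advanced gastric cancers) in real time". ENDOANGEL-GC combines lesion detection with blind-spot monitoring.
- **Procedures.** In the experimental group only, "lesions marked in red boxes by ENDOANGEL-GC are required to undergo biopsy sampling".
- **Specimen management and pathological traceability.** For patients with cancer on biopsy, or highly suspected without biopsy, "their pathological results of resected specimens will be traced for up to 60 days from their endoscopy date". No search for cancers missed at the examination is described.
- **Sample size calculation.** One cancer proportion, 1%, serves both arms. The assumed effect is given as "resulting in an estimation that the EGC detection rate will increase from 20% to 35% with AI assistance". This outcome sets the trial size at 30,000; the neoplasm outcome alone needs 4,858.

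**The concern.** Randomisation takes place before the examination, and the examination decides who counts as a gastric cancer patient. The EGC test therefore compares two subgroups formed after randomisation by what each arm found. The data analysis plan defines the intention-to-treat population as everyone randomised, but this ratio cannot use that population as its denominator.

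The Introduction states the hypothesis as better detection of neoplasms and of EGC. A share of detected cancers answers a different question. Each extra early cancer enters both numerator and denominator, and each extra advanced cancer lowers the share. A real gain in early cancers can be hidden, and the share can move with no change in early cancers at all. Since this outcome sets the trial size, the main EGC conclusion is at stake.

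**Working it through.** **1. The plan's own figure.** Inputs: 20% vs 35%, two-sided α 0.05, power 80%, 1:1.

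n per arm = [1.96·√(2·0.275·0.725) + 0.842·√(0.20·0.80 + 0.35·0.65)]² / 0.15² = 137.9, so 138 per arm and 276 in total. With unpooled variance it is 136 per arm, 272 in total. The stated 270 lies within 3% of both, and power at 135 per arm is 79%. Then 270 / 0.01 / 0.9 = 30,000. The sizing reproduces, so the problem lies in the endpoint and not in the arithmetic.

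**2. Expected control arm.** 30,000 × 0.9 / 2 = 13,500 evaluable. At 1%, that gives 135 cancers: 27 early (20%) and 108 advanced. EGC per randomised patient is 27 / 13,500 = 0.20%.

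**3. Scenarios for the AI arm.** Power is the chance of a significant result in favour of the AI, from a two-proportion z test. Ranges are pooled to unpooled variance. The multipliers on advanced cancers are assumptions.

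| Assumed AI effect | Early + advanced | EGC share | Power, share | EGC per randomised | Power, per randomised |
|---|---|---|---|---|---|
| Both ×1.8 | 48.6 + 194.4 | 20.0% | 2.5% | 0.36% | 70% |
| Early ×1.8, advanced ×1.25 | 48.6 + 135 | 26.5% | 26–28% | 0.36% | 70% |
| Early ×1.8 only | 48.6 + 108 | 31.0% | 57–59% | 0.36% | 70% |
| Early ×2.15 only | 58.2 + 108 | 35.0% | 83–84% | 0.43% | 92% |
| 135 cancers, 35% early | 47.25 + 87.75 | 35.0% | 79–80% | 0.35% | 65% |

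In the first row the AI arm finds 48.6 − 27 ≈ 22 more patients with EGC, and the share does not move.

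**4. Movement with no change in EGC.** With 27 early cancers in both arms, 20 fewer advanced cancers give 27 / 115 = 23.5%. Advanced ×1.25 gives 27 / 162 = 16.7%. Neither change says anything about early detection.

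**5. What the single 1% implies.** If both arms have 135 cancers and the share is 35%, the AI arm has about 47 early and 88 advanced, about 20 fewer advanced than control. If instead the advanced count stays at 108, a 35% share needs 0.35 × 108 / 0.65 ≈ 58 early and 166 cancers in all, and 1% no longer holds in that arm. The plan does not say which is meant.

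**6. Behaviour under no effect.** Simulating independent Poisson counts with means 27 and 108 in both arms gives a two-sided rejection rate of about 5%.

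**The case against.** A reader might infer that the EGC comparison is invalid because its denominator arises after randomisation. That goes too far. If the AI changes nothing, randomisation balances early and advanced counts alike and the test keeps its size. The difficulty is interpretation once there is an effect.

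A reader might also infer that the ratio will miss a benefit. The documents do not support that. They give no figure for a rise in advanced-cancer detection. The improvement of more than 80% in the sample size section concerns EGC sensitivity and proportion, and the Introduction says what the earlier system can diagnose, not that it raises the yield of advanced cancers. Nor does anything suggest that the AI suppresses advanced detection. If only EGC rises, the ratio moves correctly and has 83–84% power at a 35% share.

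Other points also stand:

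- The neoplasm outcome would register the worst case. If cancers rise by 80% and other neoplasms do not change, 2.5% becomes 2.5% + 0.8 × 1% = 3.3%, with about 97% power at 13,500 per arm. The trial would not look negative overall, but this result would not isolate EGC.
- The ratio is a disclosed choice, and its control value comes from cited studies reporting an EGC detection rate.
- It is tempting to say that the numerator is not a subset of the denominator, because the pathology scheme lists high-grade intraepithelial neoplasia apart from carcinoma. But the Outcomes section says "EGC includes pathologically proven high-grade intraepithelial neoplasia and gastric cancer restricted to the mucosa and submucosa", and EGC is naturally read as part of gastric cancer. A clarifying phrase is enough.
- Contrasting 270 cancers with 30,000 patients overstates the gain in information. With rare events the event count governs precision, and a per-randomised comparison at ×1.8 rests on about 27 + 49 early cancers.
- More than 10,000 patients were already enrolled, endoscopists are unmasked and there is no data monitoring committee, so changing a registered primary has a credibility cost.

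**Conclusion.** The concern holds as a fault of interpretation. The definition is fixed in the Outcomes section and is not a detail awaiting the analysis plan. Once the AI has any effect, a change in the ratio cannot be attributed to early detection without knowing what happened to advanced detection, and a flat ratio cannot be read as no gain.

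For an 80% rise in early cancers, the power of the ratio runs from 2.5% (advanced up equally) through 26–28% (advanced up 25%) to 57–59% (advanced unchanged), while the per-randomised rate has 70% throughout. The size rests on the plan's 1%, 20% and 10% dropout and on assumed changes in advanced detection. In one case the ratio has the higher power: 135 cancers per arm with 35% early gives 79–80% against 65%. That advantage depends on about 20 fewer advanced cancers in the AI arm. The neoplasm outcome is unaffected.

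**What to change.** By a dated amendment made blind to outcome data by arm, specify as the confirmatory EGC analysis the number of patients with EGC (high-grade intraepithelial neoplasia, or cancer confined to mucosa or submucosa) divided by all patients randomised to the arm. Report the EGC share of gastric cancers beside it as descriptive, and state that high-grade neoplasia counts in both its numerator and its denominator.

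If the registered ratio must stay primary, pre-specify the per-randomised rate as a key secondary outcome, report advanced-cancer counts by arm, and draw no claim of improved EGC detection from the ratio alone.

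**Cost.** The data are already collected and no extra patients are proposed; the protocol, registry and analysis plan wording changes. A mid-trial change to a registered endpoint must be disclosed. If the per-randomised rate becomes confirmatory, the stated 80% power no longer applies. With 30,000 randomised and 13,500 evaluable per arm, it is about 65% for 0.20% vs 0.35%, 70% for 0.20% vs 0.36%, and 92% for 0.20% vs 0.43%. In the first case 80% power would need 19,133 per arm, or 38,266 / 0.9 ≈ 42,518 in all, so the shortfall should be stated openly.

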## Study withdrawal

Eligible participants will be included in this study after providing informed consent and undergoing randomisation. The participants can withdraw at any time during the study. Data collected prior to withdrawal can be used in this study if informed consent is obtained. Participants should be withdrawn in the following situations: (1) perforation, (2) massive haemorrhage, (3) allergy to sedative medication, (4) poor preparation, and (5) gastric retention. Withdrawn participants will not be replaced by other recruited participants after they sign the informed consent form.

## Safety evaluation

Adverse events are evaluated according to the Common Terminology Criteria for Adverse Events [20]. Occurrence time, expiration time, interventions, and treatments will be recorded.

## Data analysis

### Sample size calculation

The sample size is calculated on the basis of the primary outcomes.

The detection rate of gastric neoplasms and EGC detection rate without AI assistance were determined by literature research. Zhang et al. reported an EGC detection rate of 20.0 to 20.9% [21] and a gastric neoplasm detection rate of 1.63%. Di et al. reported an EGC detection rate of 16.44% and a gastric neoplasm detection rate of 3.37% [22]. Therefore, the EGC detection rate in the control group is estimated to be 20%, and the gastric neoplasm detection rate is estimated to be 2.5% (the mean value of the two references).

According to our previous study, the detection rate of gastric neoplasms increased by 1.35% when assisted by an AI system; therefore, the detection rate of gastric neoplasms in the experimental group is estimated to be 4.0%. There are no published data evaluating the improvement in EGC detection rates with AI assistance. Thus, we referred to two studies reporting improvements of > 80% in EGC detection sensitivity and proportion [23, 24], resulting in an estimation that the EGC detection rate will increase from 20% to 35% with AI assistance.

The sample size was calculated, using the *Z* test method, as 4858 based on the detection rate of gastric neoplasms, with a two-sided *α* level of 0.05 and power of 80%, allowing for 10% drop-out rate. Regarding the sample size based on the EGC detection rate, the *Z* test method was used for calculation with a two-sided *α* level of 0.05 and power of 80%, resulting in a total of 270 cases of gastric cancer. Assuming the proportion of gastric cancer to be 1% in patients undergoing EGD and allowing for a 10% dropout rate, the sample size was calculated as 30,000. Considering the larger sample size calculated from the two primary endpoints, the required sample size was determined to be 30,000.

To achieve adequate participant enrolment, we first evaluated the annual volume of sedated EGD examinations at all participating centres. The sum of the examination volumes of all centres (> 20,000 per year) is sufficient to provide support for the completion of the study. In each centre, a study coordinator, group of nurses, or endoscopists will be pretrained for informed consent before the examination. Consecutive patients will be informed about the study and assessed for eligibility.

### Data collection

Data will be collected in a standard case-report form through the EDC system and anonymised for further analysis. Data include baseline information, endoscopic reports, and pathological results. Data will be de-identified before being entered into the database. Regular quality monitoring and database checking will be performed at each centre to ensure data accuracy.

In addition, the computer on which the ENDOANGEL-GC runs will be equipped with video-recording software. It is used to capture and store video signals from the endoscope device and predictions from the ENDOANGEL-GC system. For each examination, an unprocessed raw video from the endoscope and a video with ENDOANGEL-GC predictions (“AI” videos) are recorded and stored.

### Data analysis plan

The analysis will use intention-to-treat (ITT) and PP approaches. The ITT population will include all patients who are randomised, whereas the PP population will include patients who undergo EGD in accordance with the assigned intervention. The null hypothesis is that the detection rates of gastric neoplasms and EGC in the experimental group will not differ from those in the control group. An alternative hypothesis is that the detection rates of gastric neoplasms and EGC in the experimental group will differ from those in the control group. The experimental group (with ENDOANGEL-GC assistance) will be compared with the control group (without ENDOANGEL-GC assistance) for the two primary outcomes using the *χ*^2^ test.

Continuous variables will be expressed as means (standard deviations [SDs]) or medians (interquartile ranges [IQRs]), according to their distributions, and categorical variables will be presented as numbers (percentages). Baseline characteristics between the two groups will be compared using the *χ*^2^ test for categorical variables and the Mann-Whitney *U* test for continuous variables. Statistical significance is set at *p* < 0.05. A 95% confidence interval will be calculated. Subgroup analysis will be conducted, stratified by multiple indices, such as age and ENDOANGEL-GC-marked red boxes, indicating that only red-box-marked lesions will be included in the analysis. The histological data and lesion characteristics will be compared with the ENDOANGEL-GC prediction, and the performance of ENDOANGEL-GC will be further analysed.

In this study, the potential missing data include the following: (1) characteristic information (the missed data will be marked with “NA” and will not be included in the analysis); (2) pathological results, the gold standards for analysis (participants with missing pathological results are excluded from the analysis); and (3) original videos (the data contained information on whether the endoscopic procedure adhered to the protocol requirements). Participants without this information will be excluded from the per-protocol analyses.

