## Randomisation

Local study coordinators or staff accomplished randomisation using an EDC system. Participants were randomised into either the experimental or control group at a 1:1 ratio before the examinations. The randomisation results, time points, and case IDs will be stored online in the EDC system.

Participants will be randomised into one of the two arms by block randomisation stratified by centre. The randomisation sequence will be developed using a computer-generated random numerical series, with one encoding for the AI-assisted group and zero encoding for the control group. The original sequence will be stored in an online central randomisation system database. The online sequence will not accessible to investigators or study coordinators. If a subject fulfils the enrolment criteria, the authorised study coordinators or staff will log in to the password-protected account to obtain the assignment for him/her.

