## Discussion

This study will explore the effectiveness of the AI system ENDOANGEL-GC in improving the detection rate of gastric neoplasms and EGC detection rate. We plan to enrol 30,000 participants from > 20 large-scale primary digestive centres in China. Enrolment began in December 2021. At the time of manuscript preparation, more than 10,000 patients had been enrolled. The results of this large, multi-centre RCT will provide high-level evidence for the application of AI systems in clinical settings.

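### Randomisation is stratified by centre, but both primary outcomes are tested by a plain chi-square with no centre term: valid, but it gives up precision on the EGC ratio if centres differ

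*Protocol article*

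**What the plan says.** The Randomisation section of the protocol article reads: "Participants will be randomised into one of the two arms by block randomisation stratified by centre". The abstract repeats it ("Block randomisation, stratified by centre"). Allocation is 1:1. The Discussion gives the scale: "We plan to enrol 30,000 participants from > 20 large-scale primary digestive centres in China".

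The Data analysis plan names one test for both primary outcomes. The experimental group "will be compared with the control group (without ENDOANGEL-GC assistance) for the two primary outcomes using the" chi-square test. Centre is not mentioned there. The only stratification in that section concerns subgroups: "Subgroup analysis will be conducted, stratified by multiple indices, such as age and ENDOANGEL-GC-marked red boxes".

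The Outcomes section gives the two primary outcomes different denominators. The neoplasm rate is taken over everyone recruited. The EGC rate is taken over patients with gastric cancer only.

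**The concern.** Centre is the one factor on which randomisation is stratified, and the stated primary analysis leaves it out. The usual principle is to analyse by the strata that were randomised, because the between-centre part of the variation can then be removed from the comparison.

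The point bears mostly on the EGC ratio, the endpoint that sets the total of 30,000. Blocks within centre balance all randomised patients. They do not tightly balance the roughly 1% who turn out to have gastric cancer. With about 270 cancers over more than 20 centres, there are fewer than 270/20 = 13.5 cancers per centre, or under 7 per arm. The centre mix of the cancers can therefore differ between arms by chance.

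Centre differences in early-stage share are plausible from the article's own procedures. Pathology is read locally, and only unmatched lesions go to independent expert pathologists. Invasion depth depends on tracing resected specimens within 60 days. At stake is power, not the false-positive rate.

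**Working it through.** **Inputs from the article.** Two-sided alpha 0.05; power 80%; neoplasms 2.5% vs 4.0%; EGC among cancers 20% vs 35%; cancer prevalence 1%; dropout 10%; more than 20 centres.

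**Assumed input.** The SD of the centre log-odds is taken as 0 to 1.0 for neoplasms and 0 to 1.5 for EGC. The article gives no value.

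**1. The plan's own sample sizes.** The two-proportion formula is n per arm = [1.960·√(2p̄(1−p̄)) + 0.842·√(p₁(1−p₁)+p₂(1−p₂))]² / (p₁−p₂)².

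- Neoplasms: p̄ = 0.0325, giving 2,193 per arm and 4,386 in total; 4,386/0.9 = 4,874, against 4,858 stated.
- EGC: p̄ = 0.275, giving 138 per arm and 276 in total. The unpooled version gives 136 per arm and 272. The article states 270.
- Total: 270/0.01 = 27,000 and 27,000/0.9 = 30,000, an exact match.

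All three figures follow, to within 3%, from formulas without a centre term. Sizing and analysis are thus consistent with each other in omitting centre.

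**2. Neoplasms, plain chi-square vs Cochran-Mantel-Haenszel (CMH) by centre.** Simulation with 20 unequal centres and arms balanced within centre. Type I error is at 27,000 patients (20,000 runs). Power is at 4,858 × 0.9 ≈ 4,372 patients (8,000 runs).

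| Centre SD | Type I error, plain / CMH | Power, plain / CMH |
|---|---|---|
| 0 | 5.1% / 5.1% | 80.1% / 80.1% |
| 0.5 | 4.6% / 4.6% | 79.9% / 80.1% |
| 1.0 | 4.7% / 5.0% | 77.6% / 78.5% |

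The gain is under 1 point. At the planned 13,500 evaluable patients per arm (27,000/2), the power of the plain test for 2.5% vs 4.0% already exceeds 99.99%.

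**3. EGC ratio, plain chi-square vs CMH.** Simulation with about 270 cancers, 20 unequal centres, random cancer counts per arm and 20,000 runs. The within-centre odds ratio is held fixed, so the overall difference, and with it the power of both tests, shrinks as the SD grows. Compare within rows.

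| Centre SD | Type I error, plain / CMH | Power, plain / CMH |
|---|---|---|
| 0 | 5.0% / 4.9% | 78.7% / 75.7% |
| 0.5 | 5.2% / 5.1% | 74.2% / 72.6% |
| 1.0 | 5.2% / 5.2% | 65.3% / 67.7% |
| 1.5 | 5.2% / 5.0% | 53.1% / 60.5% |

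CMH loses at small spread, because centres with very few cancers contribute little or nothing to it.

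**4. EGC ratio, adding a random-centre logistic model.** Simulation with 270 cancers, 22 unequal centres, overall rates held at 20% vs 35%, a likelihood-ratio test for arm and 1,500 runs per setting. The last column is a repeat run, rounded.

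| Centre SD | Power, plain / CMH / random centre | Repeat run |
|---|---|---|
| 0 | 79.4 / 75.8 / 79.7% | 80 / 78 / 80% |
| 0.5 | 80.9 / 79.4 / 81.3% | 78 / 77 / 80% |
| 1.0 | 77.8 / 81.5 / 82.8% | 78 / 81 / 82% |
| 1.5 | 80.1 / 87.2 / 88.3% | 80 / 87 / 88% |

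Type I error was 4.0% to 5.8% for all three methods. Gain of the random-centre model over the plain test:

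- SD 0: 79.7 − 79.4 = 0.3 points (0 in the repeat).
- SD 0.5: 81.3 − 80.9 = 0.4 (2 in the repeat).
- SD 1.0: 82.8 − 77.8 = 5.0 (4 in the repeat).
- SD 1.5: 88.3 − 80.1 = 8.2 (8 in the repeat).

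The Monte Carlo standard error of one power figure is about √(0.8 × 0.2/1,500) = 1.0 point, so small differences between the runs mean nothing.

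**The case against.** The strongest case for leaving the plan alone is that nothing is invalid. The plain test holds its level, and for neoplasms the gain is negligible at the planned size. For EGC, the textbook stratified test does worse than the plain one when centres differ little. All of this stands. It limits the point to efficiency and rules out strict CMH for the EGC ratio. It does not count against a random-centre model, which showed no loss at SD 0.

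It can also be said that the article condenses a fuller protocol, and that centre-adjusted supportive analyses may sit in an analysis plan not shown. That may be so. But the article itself names the primary test, so this is a stated choice and not a missing detail.

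A reader might infer more than the documents support:

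- **That the plan targets a diluted odds ratio.** It names no odds ratio. The outcomes are proportions and the hypotheses concern detection rates.
- **That the standard errors are wrong, or that chance centre imbalance biases the EGC comparison.** The standard error covers chance imbalance, as the type I error near 5% shows.
- **That the cited neoplasm rates of 1.63% and 3.37% show between-centre spread.** They come from two separate publications, not from this trial's centres.
- **That EGC should therefore be counted per randomised patient.** That would change a primary outcome. It is a separate question, which adjusting for centre neither needs nor settles.

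**Conclusion.** The point holds as one of efficiency and of matching analysis to design. The plain chi-square is valid, at worst slightly conservative for neoplasms, and no sample size changes.

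The possible gain is concentrated in the EGC ratio: about zero if centres are alike or differ moderately, and roughly 5 to 8 power points if the SD of the centre log-odds is 1.0 to 1.5. An SD of that size is large, and nothing in the article shows that it applies. The figures also assume unequal centre sizes, normal centre effects on the logit and about 270 cancers.

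The change is worth making because it costs almost nothing if centres are alike and protects the endpoint that sets the trial's size if they are not. It is a recommended improvement, not a condition for the trial's validity.

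**What to change.** Amend the Data analysis plan before unblinding:

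- **Gastric neoplasms.** Make the primary test a Cochran-Mantel-Haenszel test stratified by centre, with a centre-stratified risk difference and 95% CI.
- **EGC ratio, as the Outcomes section defines it.** Use logistic regression with arm as a fixed effect and centre as a random effect, tested by likelihood ratio. Report the two observed proportions beside it. Do not use strict CMH here: in these simulations it lost about 2 to 4 points at SD 0 and 1 to 2 points at SD 0.5.
- **Sensitivity.** Keep the plain chi-square for both outcomes.

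The cost is wording only. The hospital is coded in the first four characters of every participant ID (Recruited case management), so no new data are needed, and the total of 30,000 stands. Data analysts are to be blinded, so the choice can still be fixed without knowledge of results. Fixing it now also avoids a later choice between two tests that might disagree.
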